## **7.3 Sample Collection**

### **7.3.1 Bone marrow samples**

Up to 20ml of bone marrow aspirate taken at 24 weeks should be sent to Cambridge Stem Cell Biobank (CBSB) in Lithium Heparin tubes. A trephine sample should also be sent in 1% paraformaldehyde in phosphate buffer using the container provided by the Trials Office. This trephine should represent the whole sample taken at the time of analysis and not cut or processed locally. This should be posted in a special delivery safe box to ensure it is received next day for processing at the central laboratory. Refer to the sample collection guidelines for further information.

### **7.3.2 Blood samples**

Peripheral blood samples to allow analysis of JAK2-V617F, CALR 5bp insertion (exon 9) and CALR 52bp deletion (exon 9) mutant allele burden should be collected in lithium heparin tubes and sent to Cambridge at baseline, 12 weeks and 24 weeks.

At baseline and 24 weeks, 60 ml of blood will be collected to allow comparison of oestrogen receptor signalling in progenitor cells.

At week 12, 30 ml blood should be obtained. The remainder of the blood not required to assess allele burden will be banked at CBSB.

The level of allele burden at 12 weeks for each patient will be provided to sites in time to inform a decision about tamoxifen dose escalation and treatment continuation beyond 24 weeks. It is not possible to provide these in real time and therefore they cannot be used as a guide for patient management.

For responder patients continuing treatment beyond 24 weeks and 36 weeks, 60 ml of peripheral blood in lithium heparin tubes should be sent to the CBSB to reassess allele burden at 36 weeks and 48 weeks, respectively. The level of allele burden observed at 24, 36 and 48 weeks for each patient will also be provided to sites to inform a decision about further tamoxifen treatment continuation. It is not possible to provide these in real time and therefore they cannot be used as a guide for patient management.

In the unlikely event that a trial blood sample is lost, damaged or mishandled so it cannot be analysed, the trial office will request another sample.

## **7.4 Dose Modifications**

Unless prevented by persistent side effects greater than grade 1, dose escalations to 40 mg tamoxifen od are encouraged, but not mandated, for patients either not showing a reduction in allele burden  $\geq 50\%$  or not showing an improvement of haematological response at 12 weeks compared to baseline.

Dose reductions to 10 mg tamoxifen od are allowed, but not mandated, for patients that develop mild/moderate side effects (grades 1-2) except for those experiencing thrombotic events, which will mandate permanent treatment discontinuation regardless of grade.

Dose modifications are only permitted on an individual basis at the discretion of the Chief Investigator/Clinical Coordinator. Please contact the Trials Office to discuss any dose changes. All changes must be recorded on the CRF.

### 7.5 Treatment Compliance

The local trial pharmacist will be responsible for maintaining and updating the drug accountability log in the pharmacy file. All unfinished packs/bottles of tamoxifen at the end of treatment/change of dose will be returned to the trial pharmacist who will count and document any unused medication. All IMP can then be destroyed in accordance with local pharmacy practice and this will be documented on the drug accountability log in the hospital pharmacy file. Refer to the Pharmacy Manual for further information.

In addition, patients will be issued with a Patient Diary at each visit as necessary for the duration of trial treatment. Patients will be asked to complete the diary, recording the time that each dose was taken, and whether any doses were missed. The diary also includes a section where the patient can record any relevant information such as side effects suffered or reasons for missed doses. The completed diary will be reviewed by the site at clinic visits and returned to the Trials Office. The patient diary will also remind patients to tell their doctor if they are receiving any other medications.

### 7.6 Supportive Treatment

Patients should continue to receive cytoreductive therapy for their MPN such as hydroxycarbamide or anagrelide, in addition to other supportive treatment such as venesection or aspirin as applicable. However, patients must not receive any treatments listed in section 7.7.

### 7.7 Concomitant Medication

Patients must not receive interferon alpha for their MPN as is known to impact in clone size. Patients can have received interferon alpha previously as long as the last dose was >6 months from trial entry.

Patients should not receive any medications contraindicated with tamoxifen according to the SPC. At the time of writing, potent inhibitors of CYP2D6 (e.g. paroxetine, fluoxetine, quinidine, cinacalcet or bupropion (refer to Appendix 8)) should be used with caution and avoided where possible.

As tamoxifen is metabolised by CYP3A4, caution is also required when co-administering with drugs such as rifampicin, and alternatives should be prescribed where possible.

In addition, tamoxifen should not be given to patients who have received it in the past and who have experienced hypersensitivity to the product or any of its ingredients.

For patients on coumarin type anticoagulants such as warfarin, an increase in anticoagulant effect can occur with tamoxifen and therefore additional monitoring is recommended.

### 7.8 Patient Follow Up

All patients will be followed up until 28 days after the last administration of tamoxifen. This applies if treatment is stopped at 24 weeks, or 28 days after the last treatment if the patient continues beyond 24 weeks. Patients stopping trial treatment early will continue to be followed up for the trial outcomes as per protocol schedule unless the patient specifically withdraws consent.

If patients discontinue study drug prior to 24 weeks, collection of blood samples for central assessment of mutant allele burden should continue to be taken at the protocol specified time points providing the patient received at least 2 months of tamoxifen treatment, and the time point is <3 months from the last date of trial treatment.

Patients continuing trial treatment beyond 24 weeks will have their mutant allele burden reassessed at 36 weeks. Patients continuing trial treatment beyond 36 weeks will have their mutant allele burden reassessed at 48 weeks.

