### Trial Duration

All patients will receive trial treatment for 24 weeks. Following 24 weeks, they will be able to continue treatment with tamoxifen if there is clinical benefit, at the discretion of the treating Investigator, and their response will be reassessed after 36 and 48 weeks of treatment as applicable. The last patient visit will be 28 days after the last administration of trial treatment.

Recruitment will be over 28 months from 13-15 trial centres. Therefore the total trial duration will be 35 months for patients receiving treatment for 24 weeks. For patients continuing treatment for 36 and 48 weeks, the total trial duration will be 38 and 41 months, respectively.

---

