| Concomitant diseases and treatment                                                                                                          |                                                 | <<Continuous throughout study>>                                                                                                     |          |                           |                |                                      |                                              |
| Adverse events                                                                                                                              |                                                 | <<Continuous throughout study>>                                                                                                     |          |                           |                |                                      |                                              |

 Can be obtained more than 6 weeks prior to registration.  To include Hb, HCT, WBC count, RBC count, Platelets, ANC, lymphocytes, blood film, eGFR/calculated creatinine clearance, ALP, AST/ALT, bilirubin, calcium, LDH.  Particular attention must be paid to gynaecological history.  For PV/ET patients that entered the trial with PR and enlarged spleen, the ultrasound at 24 weeks will be performed earlier if a CR is suspected.  This applies to 28 days after 24 weeks of treatment or 28 days after the last treatment if patient receives treatment for more/for less than 24 weeks.  Please refer to section 7.2.9.  Please refer to section 7.4 for dose modification rules.  For patients continuing treatment beyond 24 weeks, mutant allele burden will be reassessed at 36 weeks. For patients continuing treatment beyond 36 weeks, mutant allele burden will be reassessed at 48 weeks. Please refer to sections 7.3.2 and 7.8 for further details.  Every effort should be made for

---

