## 3. TRIAL DESIGN

This is a single arm, open label, multicentre, phase II trial of tamoxifen in patients with MPNs.

The aim of the study is to evaluate the activity of tamoxifen in terms of reducing allele burden and the safety of giving tamoxifen in this group of patients. A single stage A'herns design has been chosen to give evidence of activity for the treatment.

All patients will receive a minimum of 24 weeks of treatment with tamoxifen at 20mg od. Patients will be seen at weeks 4, 12, 18 and 24. Mutant allele burden of JAK2-V617F, CALR 5bp insertion (exon 9) and CALR 52bp deletion (exon 9) will be assessed at baseline. Allele burden will be reassessed at 12 weeks and 24 weeks for the mutation(s) identified at baseline. Patients may continue treatment

beyond 24 weeks at the discretion of the treating Investigator. If patients do continue treatment they should be followed up a minimum of 12 weekly and their allele burden reassessed at 36 weeks and 48 weeks as applicable. All patients will be followed up until 28 days after the last dose of tamoxifen treatment.

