#### 7.2.7 Bone marrow evaluation

Patients will be required to undergo a bone marrow aspirate and trephine biopsy 24 weeks after starting treatment with tamoxifen. This will be assessed centrally for response using IWG-MRT Criteria (Appendix 6) for MF patients and 2013 ELN Criteria (Appendix 7) for ET/PV patients.

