### 7.9 Patient Withdrawal

In the event of discontinuation of study treatment, e.g. unacceptable toxicity or patient choice, full details of the reason/s for discontinuation should be recorded on the CRF.

All patients, including non-compliant subjects, should be followed up according to the protocol schedule unless they withdraw specific consent.

In the event of a patient's decision to withdraw from the trial, the Investigator should ascertain from which aspects of the trial the patient wishes to withdraw and record the details on the appropriate CRF. All information and blood/bone marrow samples collected up until the point of retraction will be retained and analysed. If a patient chooses to withdraw from treatment only, the patient should discontinue treatment and continue to be assessed in accordance with the protocol. If a patient wishes to withdraw from the trial (i.e. including trial specific assessments), but is willing for further data to be supplied to the Trials Office, then further routine 'follow-up' data (e.g. toxicity data) will continue to be supplied by the Investigator to the Trials Office.

Patients who stop treatment due to adverse experiences (clinical or laboratory) will be treated and followed according to accepted medical practice. All pertinent information concerning the outcome of such treatment must be recorded in the CRF.

The following are justifiable reasons for the Investigator to stop study treatment:

- Unforeseen events: any event which in the judgement of the Investigator makes further treatment inadvisable
- Serious violation of the trial protocol (including persistent patient non-attendance and persistent non-compliance)
- Stopping by the Investigator for clinical reasons not related to the study drug treatment

Patients must stop study treatment in the event of:

- Unacceptable toxicity, defined as:
  - Grade 3-4 adverse event considered related to the trial IMP
  - Persisting grade 1-2 adverse events considered related to the trial IMP lasting more than 14 days and that do not resolve within 4 weeks of reducing tamoxifen to 10 mg od
- Thrombotic event of any grade
- SAE requiring permanent discontinuation of treatment
- Transformation to MDS or AML

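### Footnote 5, Section 3 and the synopsis end the study 28 days after the last dose, but 7.8 and 7.9 keep early stoppers on schedule, so week-24 data after a stop before week 20 depend on which text a site follows

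*Combined protocol and SAP*

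**What the plan says.** Three places end the study by reference to the last dose.

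- Section 3 (Trial Design): "All patients will be followed up until 28 days after the last dose of tamoxifen treatment".
- Synopsis, Trial Duration: "The last patient visit will be 28 days after the last administration of trial treatment".
- Schedule of Events, footnote 5, attached to the end-of-study column: 28 days after 24 weeks of treatment, or "28 days after the last treatment if patient receives treatment for more/for less than 24 weeks". This is the only one of the three that names patients treated for less than 24 weeks.

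Two places keep patients who stop early on the planned visits.

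- Section 7.8: "Patients stopping trial treatment early will continue to be followed up for the trial outcomes as per protocol schedule", unless the patient withdraws consent.
- Section 7.9: "All patients, including non-compliant subjects, should be followed up according to the protocol schedule unless they withdraw specific consent".

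Section 7.8 also opens with a 28-day rule, but its second sentence limits the scope: "This applies if treatment is stopped at 24 weeks, or 28 days after the last treatment if the patient continues beyond 24 weeks". Patients who stop before week 24 fall outside that sentence.

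For one item, the allele-burden blood sample after an early stop, 7.8 sets its own condition. The sample is still taken "providing the patient received at least 2 months of tamoxifen treatment, and the time point is <3 months from the last date of trial treatment".

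**The concern.** The primary outcome compares week-24 allele burden with baseline. Response category and improvement in category are also assessed at week 24, as is one of the two haematological response time points. These assessments are timed from the start of treatment, not from the last dose; for the marrow, 7.2.7 says "Patients will be required to undergo a bone marrow aspirate and trephine biopsy 24 weeks after starting treatment with tamoxifen". A closing visit timed from the last dose can therefore fall before them.

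The closing visit does not replace week 24. Its column in the Schedule of Events lists the medical examination, haematology and biochemistry, and haematological response. It lists no allele-burden blood, marrow, ultrasound or MPN-SAF.

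Under 7.9, a related grade 3-4 event or a thrombotic event of any grade requires treatment to stop. The group with conflicting instructions is therefore defined partly by toxicity. With 13 to 15 centres, whether that group has week-24 data could vary with the page each site works from.

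**Working it through.** **Inputs.** Closing visit 28 days (4 weeks) after the last dose: footnote 5, Section 3, synopsis. Outcome visit at week 24: Schedule of Events and Section 12.1. Sampling condition of at least 2 months treated and less than 3 months since the last dose: 7.8. Primary sample window of week 24 plus or minus 4 weeks: 12.1.1. Assumption: one month is 30.4375 / 7 = 4.35 weeks, so 2 months = 8.7 weeks and 3 months = 13.04 weeks.

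**The plan's own figure.** Section 12.6 gives 42 patients and a rule of 3 or more responders, for 2% against 10%, one-sided alpha 0.1 and 80% power. With P(X ≥ 3) = 1 − Σ C(42, x) pˣ (1 − p)⁴²⁻ˣ over x = 0, 1, 2, the exact alpha at p = 0.02 is 0.0515 and the exact power at p = 0.10 is 0.8049. A search confirms 42 as the smallest size meeting both limits (41 gives power 0.7914). The design reproduces, and nothing below changes it.

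**Where the rules disagree.** The closing visit falls before week 24 when stop week + 4 < 24, that is, for stops before week 20.

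**Where the primary sample is caught.** Under 7.8, week-24 blood is due only if 24 − stop week < 13.04, so the stop must come after week 24 − 13.04 = 10.96. That already exceeds the 8.7-week minimum. The sample is both due under 7.8 and cut off by footnote 5 for stops at about weeks 11 to 20.

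| Last dose | Closing visit under footnote 5 | Week-24 items due under 7.8 and 7.9 | Missed if footnote 5 is followed |
|---|---|---|---|
| Before about week 11 | Before about week 15 | Marrow, ultrasound, MPN-SAF, response; no allele sample | Marrow, ultrasound, MPN-SAF, response |
| About week 11 to before week 20 | About week 15 to before week 24 | The same, plus allele sample | All of these, including the primary-outcome sample |
| Week 20 or later | Week 24 or later | All | None |

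The ultrasound entry excepts PV/ET patients whose scan was brought forward under 7.2.3.

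**Example.** Last dose at week 13. Footnote 5 closes the study at week 13 + 4 = 17. Week 24 is 24 − 13 = 11 weeks after the last dose, inside 13.04, so 7.8 requires the sample. Week 17 also precedes the opening of the primary window at 24 − 4 = week 20.

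**12-week allele burden.** That sample is due only after 8.7 weeks of treatment. A stop at 8.7 weeks puts the closing visit at 8.7 + 4 = 12.7, after week 12. An earlier stop owes no sample under 7.8. The conflict never changes this outcome.

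**What a missing result would cost.** The number is not in the documents. If k patients had no week-24 result and could not count as responders, and the rest responded at 10%, power would be 77.7% for k = 2 and 74.6% for k = 4. These values of k are assumptions, and the figures are upper bounds on the loss from this conflict, because 7.8 itself excludes some samples under either reading.

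**The case against.** The best defence is that the sections written for this situation agree. Sections 7.8 and 7.9 both keep early stoppers on schedule, and 7.9 repeats this for patients who withdraw from treatment only. What differs is summary text and one footnote, and the footnote could be read as merely timing the 28-day safety visit without cancelling week 24.

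This shows which reading was probably intended, but it does not remove the conflict. The column is labelled as the end of the study, the footnote expressly includes treatment shorter than 24 weeks, and 7.8 sends sites to the schedule where that footnote stands.

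The 4-week primary window helps less than it seems. For stops from week 16 the closing visit falls at week 20 or later, inside the window, but no allele-burden blood is listed for that visit. Central monitoring (10.3) would catch some omissions, although staff check forms against a protocol that supports both readings. Secondary outcomes are described as descriptive, which limits the harm there but does not bear on the primary sample.

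The defence succeeds against several stronger inferences:

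- That 7.8 contradicts itself. Its second sentence limits the 28-day rule to patients who reach week 24.
- That the 2-month and 3-month conditions are part of the contradiction. They are an explicit rule for one sample. Removing them would add samples that 7.8 excludes, which is a separate design question.
- That a week-24 marrow without an allele sample serves no purpose. It feeds the response category, and Appendices 6 and 7 do not require molecular response for that.

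**Conclusion.** The conflict stands in the current text: footnote 5, Section 3 and the synopsis against 7.8 and 7.9. It affects week-24 marrow, ultrasound, MPN-SAF and response assessment for stops before week 20, and the primary-outcome sample for stops at about weeks 11 to 20. The lower limit rests on a calendar month of 4.35 weeks. If 3 months were taken as 12 weeks, it would be 24 − 12 = week 12. Stops from week 20 onward and the 12-week allele-burden outcome are untouched.

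A reader might apply the 7-of-21 intolerance trigger in 12.4 to all 42 patients, get 14, and set that against the rule of 3 responders. The documents do not support this. The trigger prompts a committee review and is not an expected stopping rate, and a count of all early stoppers includes many outside the affected weeks. No threat to the go decision has been shown. What is shown is that the plan gives sites two answers on whether outcome data are collected, and that following one of them loses data the other requires.

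**What to change.** Reconcile footnote 5, Section 3 and the Trial Duration paragraph of the synopsis with 7.8 and 7.9. Each should state that, for a patient who stops tamoxifen before week 24 without withdrawing consent, the visit 28 days after the last dose does not end follow-up. Outcome assessments continue to week 24, with allele-burden sampling under the conditions already in 7.8. Distinguishing the 28-day post-treatment visit from the end of study in the column heading would help.

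The cost is wording in three places and some off-drug visits that 7.8 and 7.9 already require. The sample size, decision rule and sampling conditions stay as they are.

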### 7.9 Patient Withdrawal

In the event of discontinuation of study treatment, e.g. unacceptable toxicity or patient choice, full details of the reason/s for discontinuation should be recorded on the CRF.

All patients, including non-compliant subjects, should be followed up according to the protocol schedule unless they withdraw specific consent.

In the event of a patient's decision to withdraw from the trial, the Investigator should ascertain from which aspects of the trial the patient wishes to withdraw and record the details on the appropriate CRF. All information and blood/bone marrow samples collected up until the point of retraction will be retained and analysed. If a patient chooses to withdraw from treatment only, the patient should discontinue treatment and continue to be assessed in accordance with the protocol. If a patient wishes to withdraw from the trial (i.e. including trial specific assessments), but is willing for further data to be supplied to the Trials Office, then further routine 'follow-up' data (e.g. toxicity data) will continue to be supplied by the Investigator to the Trials Office.

Patients who stop treatment due to adverse experiences (clinical or laboratory) will be treated and followed according to accepted medical practice. All pertinent information concerning the outcome of such treatment must be recorded in the CRF.

The following are justifiable reasons for the Investigator to stop study treatment:

- Unforeseen events: any event which in the judgement of the Investigator makes further treatment inadvisable
- Serious violation of the trial protocol (including persistent patient non-attendance and persistent non-compliance)
- Stopping by the Investigator for clinical reasons not related to the study drug treatment

Patients must stop study treatment in the event of:

- Unacceptable toxicity, defined as:
  - Grade 3-4 adverse event considered related to the trial IMP
  - Persisting grade 1-2 adverse events considered related to the trial IMP lasting more than 14 days and that do not resolve within 4 weeks of reducing tamoxifen to 10 mg od
- Thrombotic event of any grade
- SAE requiring permanent discontinuation of treatment
- Transformation to MDS or AML

